#### Limitations of DIZZTINCT-1 for scaling up

DIZZTINCT-1 had limitations that need to be addressed before widespread dissemination [29]. Low provider participation at non-academic facilities was a major issue. Academic facilities had higher participation presumably due to the learning culture and routine education activities. Providers suggested refining and enhancing the strategy to make it more convenient and resourceful. DIZZTINCT-1 did not assess patient outcomes, which will be evaluated in DIZZTINCT-2. DIZZTINCT-2 enhances the CME session, expands clinical topics, incorporates patient-oriented materials, and captures patient-oriented outcomes during follow-up.

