### Trial design {8}

We will conduct a stepped-wedge, randomized clinical trial of a multi-faceted educational and care-process based intervention designed to improve the guideline-concordant care of patients with BPPV in the emergency department. The overall design includes an ED-level implementation and embedded, patient-level dissemination strategies which will allow evaluation of both implementation and effectiveness outcomes. Our study design and proposed methods are aligned with methodological standards in a stepped wedge, randomized clinical trial. The overall study period will be approximately 24 months. The study will start with a 6-month pre-intervention period. This will be followed by staggered intervention at the 15 EDs in 11 waves (some medical centers will be paired based on the medical service area) and then an approximately 6-month post-intervention period. The order that each ED receives the intervention will be randomized. The intervention will be provided as a complete package during the month each hospital is randomized. Concurrently, patients will be recruited before and after the physician level intervention is implemented at each ED. Enrolled participants will complete a survey to obtain baseline information and then randomized individually, stratified by sex, age, and medical center, to the intervention or control arm using central computerized randomization. The intervention arm will be sent intervention materials via patient specified preferred electronic communication. The control arm will be provided with the hospital’s standard post-discharge materials.

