### Sample size {14}

#### ED level

The Kaiser Permanente Southern California study site is comprised of 14 ED facilities, which collectively had nearly 40,000 dizziness visits in 2017. We plan to collect data on these visits for approximately 24 months. Thus, for the ED-level strategy, we will evaluate documentation of the DHT and CRM in >80,000 dizziness visits anticipating an increase in volumes over time. We hypothesize that the proportion of target visits with DHT/CRM documentation will increase from 7% in the pre-intervention period to 17% in the post-intervention period based on the findings in our estimated target population in DIZZTINCT-1. Even small absolute increases in the frequency of use of the DHT/CRM in the target population are considered clinically meaningful because the DHT and CRM are simple from a resource standpoint, not expensive, low risk and highly effective in clinical trials. With a sample of 80,000 visits, our power to detect an increase in DHT/CRM use from 7% in the control visits vs 17% in the intervention visits will be effectively 100% based on a two-sided test for independent proportions considering clustering at 14 sites, an intraclass correlation coefficient (ICC) by provider of 22% for provider-level variability (from DIZZTINCT-1) and a significance level of 5% (Table 1). We will use a mixed effects model to account for secular trends, hospital- and provider-specific features, and the potential relative association of the various components with the outcome. We estimate that 20% of the annual sample is the target population (80,000 × 0.20 = 16,000 visits) based on best available evidence that showed about 20% of dizziness patients in a national sample have BPPV characteristics. Of the 16,000 visits, approximately 8000 will be pre-intervention visits and 8000 post-intervention visits. With these volumes, we expect 560 (8000 × 7%) visits with DHT/CRM documentation in the pre-intervention period and 1360 (8000 × 17%) in the post-intervention period. Thus, we anticipate at least 1900 visits with DHT/CRM documentation. For modeling purposes, we should be able to easily meet and exceed the general rule of having 10 outcomes for each independent variable to avoid over-fitting. The large number of visits and anticipated outcomes will allow us to more closely examine differences at hospitals and provider types, and the relative influence of the various intervention components. We will be able to monitor use of the CME session, website, app, and reminder system and incorporate these variables in the model specific to the provider. The additional power will allow us to examine differences at hospitals and provider types, and the relative influence of the various ED-level implementation strategies.

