ICC for Aim 2 power patient-level intervention is at the ED-level since this is where more clustering will occur in Aim 2.

To calculate power for how the ED-level intervention impacts the patients enrolled in the trial (and thus contributing a DHI, in contrast to the larger cohort of patient only contributing data from the electronic health record) (Table 2), our calculations were made by including the number of clusters (12 ED facilities) and cluster heterogeneity using the ICC (1.9%) (Table 3). For this comparison, we have a power of 0.89 to detect a 15% difference in DHI outcome (35.7 vs 42) with our target sample size of 200 per group (Table 3). To achieve power of 0.80, we would only need 132 patients per group.

**Table 3 Tab3:** Power calculations for ED-level intervention differences in dizziness handicap inventory outcome in intervention vs control population

**Control, mean outcome (DHI*)**	**Intervention, mean outcome (DHI*)**	**Outcome difference b/t treated and control**	**SD**	**Alpha**	**ICC**	**Power for 400 subjects (200 per group)**	**Minimum sample size for power >0.8**
42	31.5	25% better	16	0.05	1.9%	1.0	96 (48 per group)
42	33.6	20% better	16	0.05	1.9%	0.99	144 (72 per group)
42	35.7	15% better	16	0.05	1.9%	0.89	264 (132 per group)

Shaded row indicates the power calculation for the prespecified threshold of a 15% difference between intervention and control groups. Calculations made considering stepped wedge design at 15 sites accounting for ICC of 1.9%

**DHI* dizziness handicap inventory. *ICC* intraclass correlation coefficient. ICC for Aim 2 power patient-level intervention is at the ED-level since this is where more clustering will occur in Aim 2

The additional power protects us against unexpected problems with recruiting or retention and also allows for additional exploratory analyses of differences in benefit based on symptom and patient characteristics.

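### The stated power of 0.89 for the ED-level effect on DHI (Table 3) comes from a parallel cluster calculation, not from the 15-ED, 11-wave stepped wedge, and the site counts conflict

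*Protocol article*

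**What the plan says.** In Sample size {14}, Patient level, Initial design, one of the two primary DHI comparisons is no intervention against ED-level intervention. The text before Table 3 says "our calculations were made by including the number of clusters (12 ED facilities) and cluster heterogeneity using the ICC (1.9%) (Table 3"). It reports "power of 0.89 to detect a 15% difference in DHI outcome (35.7 vs 42) with our target sample size of 200 per group" and adds "To achieve power of 0.80, we would only need 132 patients per group". For a 20% difference the table gives a minimum of "144 (72 per group"), and for a 25% difference 48 per group. The footnote to the same table reads "Calculations made considering stepped wedge design at 15 sites accounting for ICC of 1.9"%.

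Elsewhere, Trial design {8} states "This will be followed by staggered intervention at the 15 EDs in 11 waves", with 6 months before the first wave and about 6 months after the last. The ED-level sample size (Table 1), which concerns the same health system, was done "considering clustering at 14 sites".

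The primary DHI model in Statistical methods {20a} has ED-level group, patient-level group, their interaction, severity at the ED visit, assessment number (1 to 4) and a random ED intercept. It lists no calendar-time term; assessment number counts weeks since the visit.

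**The concern.** One calculation cannot have used both 12 and 15 clusters, and the text describes nothing specific to a stepped wedge. In a stepped wedge each ED supplies both control and intervention patients, and intervention status is tied to calendar time. The months when every ED is control, or every ED is intervention, contribute little once calendar time is modelled. A formula that treats control and intervention EDs as separate and concurrent ignores both features. Readers would judge a null ED-level DHI result against the printed 0.89. The protocol also relies on surplus power in this comparison as protection against recruitment and retention problems and for exploratory analyses.

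**Working it through.** **Inputs from the protocol.** Means 42 and 35.7 (difference 6.3), 33.6 (8.4) and 31.5 (10.5); SD 16; ICC 0.019; alpha 0.05; 200 per group in two of four groups, 800 in all; 15 EDs; 11 waves; 6 months before and about 6 after. **Assumed:** two-sided test, monthly waves, four waves of two EDs, equal recruitment per ED-month, one unadjusted DHI value per patient.

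**Step 1. Reproduce Table 3.** Parallel comparison with k = 12 clusters in each arm and m patients per cluster:
- design effect = 1 + (m − 1) × 0.019
- effective n per arm = 12m / design effect
- SE = 16 × √(2 / effective n)
- power from the noncentral t with 2k − 2 = 22 df

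| Difference | m | n per group | Power | Power at m − 1 |
|---|---|---|---|---|
| 10.5 | 4 | 48 | 0.848 | 0.743 |
| 8.4 | 6 | 72 | 0.820 | 0.755 |
| 6.3 | 11 | 132 | 0.800 | 0.768 |

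Example, last row: design effect 1 + 10 × 0.019 = 1.19; effective n = 132/1.19 = 110.9; SE = 16 × √(2/110.9) = 2.148; 6.3/2.148 = 2.93; power 0.800.

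These are the three minimum sizes in Table 3. The 0.89 is matched only approximately: 0.902 at 16 per cluster (192 per group) and 0.910 at 200 per group. Other parallel versions come close to 0.89 but miss the minimum sizes. Twelve clusters in total with a normal test gives 0.873 and a minimum of 150 per group. Fourteen in total gives 0.891, with minimums of 42, 70 and 140.

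**Step 2. Could it be a stepped wedge?** With 12 or 15 EDs and one period before the first step, power at 400 patients is 0.69–0.82 with period effects and 0.96–0.97 without. At 264 patients it is 0.53–0.67 and 0.87–0.89. No variant tried gives 0.89 at 400 together with 0.80 at 264.

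**Step 3. The actual layout.** 6 + 11 + 6 = 23 months and 15 EDs make 345 ED-months. With m patients per cell, the cell means of one ED have covariance V = [SD²(1 − ICC)/m] I + ICC × SD² J. Information for the fixed effects is the sum over EDs of X′V⁻¹X. The SE is the root of the matching diagonal element of its inverse, and power = Φ(6.3/SE − 1.96). The contrast is the ED-level effect in patients without the patient intervention. "All" below means the four-group model with interaction.

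| Patients fitted | SD | Calendar time | SE | Power |
|---|---|---|---|---|
| 400 (two groups only) | 16 | month | 2.951 | 0.57 |
| 400 (two groups only) | 16 | linear | 2.747 | 0.63 |
| 800 (all) | 16 | month | 2.411 | 0.74 |
| 800 (all) | 16 | linear | 2.276 | 0.79 |
| 800 (all) | 16 | none | 1.603 | 0.98 |
| 1,500 (all) | 16 | month | 1.790 | 0.94 |
| 1,500 (all) | 16 | linear | 1.685 | 0.96 |
| 1,500 (all) | 20 (assumed) | month | 2.238 | 0.80 |
| 1,500 (all) | 20 (assumed) | linear | 2.107 | 0.85 |

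Example, third row: 6.3/2.411 = 2.613; 2.613 − 1.960 = 0.653; Φ(0.653) = 0.743. Moving the paired EDs among the waves changes the monthly results to 0.70–0.78 (800) and 0.52–0.62 (400).

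**Step 4. Sensitivity.** An ICC from 0.001 to 0.05 moves the 800-patient monthly figure only from 0.77 to 0.74. If repeated assessments and baseline adjustment cut the variance by 30% (assumed), 0.74 becomes 0.88.

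**The case against.** A reader might infer that the trial had only 0.57 to 0.63 power for this comparison and is badly underpowered. The documents do not support that.

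- Those figures fit 400 patients alone. The stated model fits all four groups, so all 800 inform the period effects.
- The DHI model as written has no calendar term, and power is then about 0.98, above 0.89. The direction of the error therefore depends on a term the plan does not list. This stands, but the higher figure assumes no secular change in DHI, which a stepped wedge cannot take for granted. The ED-level section itself plans to account for secular trends.
- Severity adjustment and four assessments add precision that the check ignores. This stands.
- The sample size was raised to a maximum of 2,000 (about 1,500 likely), partly to secure sampling before and after the intervention at each site. The revision also says power was probably below the pre-trial assumptions, and Table 3 sits under Initial design. This removes much of the practical harm, but no replacement figure is given.
- The 23-month, even-recruitment calendar is illustrative. Recruitment accelerated, and enrolment ran from November 2022 to March 2025.

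It is also tempting to attack the ICC, since it comes from DIZZTINCT-1 and "DIZZTINCT-1 did not assess patient outcomes, which will be evaluated in DIZZTINCT-2". It is therefore not a DHI ICC, but it is openly borrowed and power hardly depends on it. A reader might also want the ED-level effect averaged over patient arms made primary. That would replace the stated comparison after enrolment has ended, with unblinded analysts, and is a choice of estimand, not a correction of arithmetic.

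**Conclusion.** The point holds as a wrong and internally contradictory power statement. The protocol gives 12 and 15 sites for the same table and 14 for the same system elsewhere. The minimum sizes are those of a parallel design with 24 separate clusters, and the footnote's claim of a stepped wedge is not borne out. The inference about the method is firm for the three minimum sizes and approximate for 0.89 itself.

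Under the assumptions listed, 0.89 overstates power at the planned 800 patients by about 0.10 to 0.15 if calendar time is modelled (0.79 to 0.74), and understates it if calendar time is left out. At about 1,500 patients power is satisfactory at SD 16 and about 0.80 to 0.85 at SD 20. The protocol says the SD was higher than expected but gives no value. Severity: should fix.

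**What to change.** 1. Reconcile 12, 14 and 15 to one site count throughout, or explain why they differ.
2. Recompute Table 3 for the actual stepped-wedge layout and calendar, with period effects and the four-group model, at about 1,500 patients, over a stated range of ICCs and of SDs above 16. State any gain assumed from baseline adjustment and repeated assessments.
3. Replace the 0.89, the minimum sizes and the footnote with the result, or label Table 3 as a superseded parallel-cluster approximation.
4. Add calendar time to the primary DHI model, so that the stated power and the analysis match.
5. Keep the stated primary comparison. The ED-level effect averaged over the two patient arms may be reported as supplementary.

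The cost is a recalculation, revised text and one model term: no patients and no new data. With calendar time in the model the ED-level estimate will be less precise than under the model as written.

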##### Sample size revised

After initiating a process change allowing patients to self-enroll into the study, recruitment in the patient level intervention accelerated. The trial leadership, in consultation with the independent medical monitor and a representative from the sponsoring institute, elected to increase the maximum sample size for this group, to ensure adequate sampling before and after the provider level intervention in each site. The increased size also allows for increased power in important subgroups (fully specified in the statistical analysis plan). Patients with either BPPV or vestibular neuritis may represent as little as 20% of the overall cohort and we anticipate most of the benefit of the patient level intervention will be in these groups. Finally, we felt that there was a low risk of having excess power. The risk of demonstrating a numeric difference in the DHI that is not clinically relevant was considered low. In addition, the non-response patterns of participants across the 4 weeks of follow up surveys for the DHI introduce another issue that could reduce the effective power of the trial. This operational decision to increase sample size was made by the trial leadership, who did not have access to the outcome data by treatment assignment at the time of the decision. Based on enrollment projections, the maximum allowed sample size was set at 2000 (based on the plan for 6 months of recruitment following the last site level intervention), although the most likely final sample size is around 1500. In addition, the standard deviation of the DHI was higher than expected—therefore power was likely lower than our pre-trial assumptions.

### Recruitment {15}

Consistent with the goals of a large, scalable, pragmatic clinical trial, there are no research personnel on site to recruit patients. Instead, once a potentially eligible participant is identified, the patients will be contacted by study staff who will introduce the study to the patient, initiate the screening process for potentially eligible participants, and engage eligible and interested patients in the consent process. We will supplement our recruitment outreach efforts with text-based and email-based outreach. These additional outreach efforts are especially important recruitment adjuncts during the COVID-19 pandemic. This text-based approach will adhere to best practices in texting, such as allowing users to reply STOP if they do not want to be contacted again. We will have a bilingual staffed research team to answer any questions patients might have during the enrollment process.

## Assignment of interventions: allocation

### Sequence generation {16a}

#### ED level

The overall study period will be approximately 24 months. After the 6-month pre-intervention period, the sites will receive the intervention in 11 waves. The order will be determined by using a random number generator. The intervention start date at each ED is the date the physicians are auto enrolled for the online CME and the printed education materials (i.e., posters, notecards) are distributed on site.

#### Patient level

Participants will be randomized individually, stratified by site, sex and age, to either the usual care (control) or enhance usual care (intervention) arms using a random number generator. Twenty-five percent of enrolled participants will be assigned to each of the 4 arms. The allocations were generated in randomly permuted block sizes for each of the strata, to limit the possibility of study staff being able to predict the next assignment. Based on the time and hospital they present to for their dizziness care, the site may or may not have received the intervention.

### Concealment mechanism {16b}

We use the randomization module of REDCAP. Participants using self-enrollment and study staff enrolling patients over the phone are unable to view the assignment prior to randomization.

### Implementation {16c}

The sizes of the randomly permuted blocks were generated by the unblinded statistician and the study recruiting staff and principal investigators were unaware of the specific details.

## Assignment of interventions: blinding

### Who will be blinded {17a}

Sites are not blinded—but they do not receive the educational materials prior to the time point specified. The individual patient participants are unaware of whether the site has received the intervention. The individual patients will receive some information from a website (either the standard educational material on dizziness or the augmented self-treatment intervention website) so they are partially blinded. The clinical investigators are blinded to response on DHI (primary patient level intervention) by treatment group, however, do review adverse events with knowledge of treatment group assignment. The data analysts are not blinded.

The participants enrolled in the patient level intervention will have additional blinding to the assigned group because both groups will receive a link to a website of educational materials. The control group will receive a link to previously developed website resources about dizziness. The intervention group will receive a link to the study’s patient educational website.

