### Composition of the data monitoring committee, its role and reporting structure {21a}

In accordance with sponsor guidelines and low risk level of study, a single independent medical monitor (IMM) with expertise in neuro-otology oversees the safety of the trial. The IMM regularly reviews the protocol, accrual information, outcomes and adverse events by treatment group and provides advice to the investigators and the sponsoring institute regarding trial continuation.

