### Adverse event reporting and harms {22}

An adverse event (AE) is any unfavorable and unintended sign (including a clinically significant abnormal laboratory finding), symptom, or disease temporally associated with the use of a medical treatment or procedure regardless of whether it is considered related to the medical treatment or procedure (attribution of unrelated, unlikely, possible, probable, or definite). Each AE is a unique representation of a specific event used for medical documentation and scientific analysis.

A serious adverse event (SAE) is an AE that is fatal or life threatening, is permanently or substantially disabling, requires or prolongs hospitalization, results in a congenital anomaly, requires intervention to prevent permanent impairment or damage, or any event that the treating clinician or internal medical monitor judges to be a significant hazard, contraindication, side effect, or precaution. Reporting serious adverse events (SAEs) are based on the guidelines of the International Conference on Harmonization (ICH).

For the purposes of the trial, we will only capture patient level AEs and SAEs that are possibly, probably or definitely related to the performance of BPPV care processes (Dix-Hallpike test or Canalith Repositioning Maneuver).

Events will be captured for the ED focused intervention by screening the medical records using natural language processing complemented by manual review of visits with DHT/CRM documentation, and subsequent medical visits with the primary diagnosis of the adverse events. For the patient facing intervention, adverse events will be captured using the same mechanisms as above, plus additional capture from patient surveys at the outcome assessment. The principal investigators are responsible for designating, at the time an AE is reported, how likely it is that the AE was caused by the study intervention. These decisions (classification of relatedness) will be reviewed by the IMM. This determination requires clinical judgment, but for purposes of this study an algorithm is used to help the investigators provide reporting that is as objective as possible and consistent with reporting across the trial.

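### Whether a procedure-related adverse event is captured depends on a relatedness rating made with knowledge of treatment group and against two different targets, so the between-group comparison is open to differential ascertainment

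*Protocol article*

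**What the plan says.** Four statements in the protocol article bear on this.

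- **Capture rule** (Adverse event reporting and harms {22}): "we will only capture patient level AEs and SAEs that are possibly, probably or definitely related to the performance of BPPV care processes", with DHT and CRM named as those processes.
- **Who rates, and against what** (same section): "The principal investigators are responsible for designating, at the time an AE is reported", the likelihood in question, namely "how likely it is that the AE was caused by the study intervention".
- **Masking** (Who will be blinded {17a}): the clinical investigators are blinded to the dizziness handicap index by treatment group, but "do review adverse events with knowledge of treatment group assignment".
- **Safeguards**: "These decisions (classification of relatedness) will be reviewed by the IMM", and "an algorithm is used to help the investigators provide reporting that is as objective as possible". Under the data monitoring item {21a}, the same independent medical monitor (IMM) regularly reviews "outcomes and adverse events by treatment group".

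AEs related to DHT/CRM are listed for both levels of the trial in Outcomes {12}.

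**The concern.** In most trials relatedness is an attribute of a recorded event, and the unrelated events remain in the tables. Here it is an entry condition. The harms section's attribution scale runs from unrelated and unlikely to possible, probable and definite, and the two lowest categories are not captured. The line between unlikely and possible is a matter of judgement, and it is drawn by people who know the group.

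The two targets make this worse. The study interventions are educational: materials, sessions and reminders for physicians, and a website for patients. Relation to a DHT or CRM can be asked of any patient who had one. Causation by the study intervention can be asked meaningfully only where that intervention was delivered. The same vomiting after the same maneuver could count in one group and drop out in the other.

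At stake is the reading of a listed outcome, and of data that the IMM uses when advising on continuation.

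**Working it through.** The document gives no expected AE count or AE rate by group, so there is no stated figure to reproduce. The check sets the passages side by side and then shows how a misrating share would carry through.

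**1. Can a qualifying event occur without the intervention?** Yes. Sample size {14} expects DHT/CRM documentation in 7% of about 8,000 pre-intervention target visits and 17% of about 8,000 post-intervention target visits:

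- pre-intervention: 8,000 × 0.07 = 560 visits
- post-intervention: 8,000 × 0.17 = 1,360 visits
- pre-intervention share: 560 / (560 + 1,360) = 560 / 1,920 = 29%

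At patient level, item {18a} asks enrolled participants whether a DHT or CRM was done at or since the visit, and whether by self, provider or other. Control participants can therefore have one too.

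**2. Does such an event meet both targets?** It meets the capture rule. Read literally, it does not meet the study-intervention wording, because no study intervention was received.

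**3. Do the raters know the group?** Item {17a} says the clinical investigators do. Item {22} gives the rating to the principal investigators. I take them to be among the clinical investigators, which is the natural reading but is not spelled out. At ED level, site and date reveal intervention status in any case.

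**4. What could unequal filtering do?** Let N1 and N0 be the numbers of procedures with and without the intervention, r a common true rate of related events per procedure, and t and c the fractions of qualifying events that pass the filter in each group. Then

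observed ratio of counts = (N1·r·t) / (N0·r·c) = (N1/N0) × (t/c).

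Per procedure, N1/N0 cancels and t/c remains. For the ED-level counts above, N1/N0 = 1,360/560 = 2.43. The values of t and c are assumptions.

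| t | c | Ratio per procedure | Ratio of ED-level counts |
|---|---|---|---|
| 1 | 1 | 1.00 | 2.43 |
| 1 | 0.75 | 1.33 | 3.24 |
| 1 | 0.5 | 2.00 | 4.86 |
| 0.75 | 1 | 0.75 | 1.82 |
| 0.5 | 1 | 0.50 | 1.21 |

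Two things follow. The direction depends on which group's events are downgraded, and the document does not fix that. And more procedures alone would raise the count in the intervention period, so in crude counts a rater effect cannot be told apart from an exposure effect.

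**5. Which outcomes pass through this filter?** Only the procedure-related AEs. Stroke hospitalizations and return visits within 30 days are listed as safety outcomes without a relatedness condition.

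**The case against.** The strongest reply is that the explicit capture rule names a procedure, not an arm, and that the later sentence is loose wording about how relatedness is designated. On that view control events qualify like any others. This stands as far as it goes. A reader might infer that control events are under-counted by construction, but that follows only if the most literal reading of the later sentence overrides the capture rule, and nothing in the document says it does. Raters could equally be lenient toward the intervention and downgrade its events.

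The safeguards are also real. A second person reviews the ratings, and an algorithm supports them. But the IMM sees AEs by treatment group and is nowhere described as masked. The algorithm is said to help a judgement that still rests with the investigators, and nothing says that it hides the group or settles which target applies. Its details may well be in the full protocol.

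Detection sources for enrolled participants are not arm-specific: "screening the medical records using natural language processing complemented by manual review of visits with DHT/CRM documentation", review of subsequent visits, plus surveys. That is correct, but the difficulty arises after detection, at classification.

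Finally, fewer control events may simply reflect fewer procedures. That is plausible, and it is a reason to remove the rater effect so that a difference can be read as exposure.

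**Conclusion.** The point holds as a risk of differential ascertainment in the comparison of procedure-related AEs between arms and periods, with unknown direction and size. It rests on three textual facts: relatedness decides capture, it is rated with knowledge of group, and the harms section gives two targets that diverge for patients who had the procedure without the intervention. It also assumes that the principal investigators are among the unmasked reviewers.

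Two stronger inferences are not supported. One is that the trial's whole safety statement is biased; stroke hospitalizations and return visits do not pass through the filter. The other is a calculated false safety signal, obtained by applying the earlier trial's figure of under 5% of visits (Supporting data) to everyone enrolled. Only participants who had a DHT or CRM can contribute such an event, the number who did is not given by arm, the denominator of that figure is not stated, and no misrating share is given. The ratios shown above are therefore illustrations, and no p-value should be attached to them.

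**What to change.** 1. **One target.** In item {22}, replace causation by the study intervention with relation to the performance of the procedure, applied identically in both arms and in both periods. The same edit should reconcile item {22} with Outcomes {12}, which at patient level also lists AEs related to gaze stabilization and walking exercises that the capture rule leaves out.
2. **Masked rating.** Have the same investigators rate, or re-rate, patient-level events from listings with arm removed, and with ED intervention status removed where feasible.
3. **Events before the filter.** For enrolled participants, tabulate survey- and record-detected events by arm irrespective of the rating, with related events as a subset. This is not asked of the more than 80,000 ED visits, where it would not be cheap.

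The cost is a wording change, masked listings and longer tables, with no additional assessor. The limits should be stated openly. Some narratives, sites or dates will reveal status, especially at ED level. Trial status gives the last enrolment as March 2025 and ratings are made when events are reported, so some events would be re-rated by people who have already seen the arm.
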